## Section 2- Background information

### 2.1 Background

The prevalence of polypharmacy, or the concomitant use of five or more drugs, has dramatically increased since the 2000s, with at least half of elderly patients meeting this definition. With such high rates, excessive polypharmacy (the use of ten or more drugs) has now emerged in at least 20% of community-dwelling elderly and is commonly responsible for adverse drug events. The frail elderly are at highest risk of excessive polypharmacy. At McGill University there recently was a cluster-randomized controlled trial, "RightRx" led by [name], examining electronic medication reconciliation software that links patient provincial drug insurance information to the in-hospital medication list. Recent (unpublished) analyses from the "RightRx" trial suggest that polypharmacy is exceedingly common amongst our elderly hospitalized patients, with more than 50% of those aged 65 and older discharged with excessive polypharmacy and 10% leaving the hospital with prescriptions for more than 20 usual daily medications. A by-product of polypharmacy is an increase in the number of drug-drug and drug-disease interactions with an increased potential for adverse drug events (ADEs). ADEs are common, with up to 35% of community-dwelling elderly having one each year. Severe ADEs contribute in up to 20% of all hospitalizations in the elderly with an associated cost of nearly 36 million dollars per year in Canada.

There is a greater risk of ADEs when a patient is taking more medications and efforts to curtail polypharmacy could reduce this risk. However, countering polypharmacy is challenging, given patients with multiple medical conditions may legitimately require medications for each condition. Nonetheless, with time, a proportion of these medications eventually become unnecessary, inappropriate, or the harms outweigh potential benefits. At this point, deprescribing via the identification and discontinuation of unnecessary or potentially inappropriate medications (PIMs), may prove to be a solution to both polypharmacy and related ADEs. Candidate medications for deprescribing can be identified using freely available, expert derived, peer reviewed lists including the: START/STOPP criteria, Beers Criteria, and Choosing Wisely Canada recommendations. All told, these lists contain hundreds of medications and because of their complexity, it is difficult for physicians to know their entire contents by memory. When deprescribing, a patient's medications are actively reviewed with specific consideration given to stopping those with an unfavorable risk-benefit profile either alone or in combination with other drugs. Despite the intuitive appeal of deprescribing, the development of an easy-to-use system that facilitates the process and that demonstrates concrete evidence of benefit and safety is required for physicians to adopt it into their everyday practice of preventive medicine.

A computer-based system could more quickly identify medications and cue the physician that deprescribing might prevent harm or prevent an adverse drug event. In this project, we have

updated our existing software, which identifies PIMs and generates instructions for the patient and physician for safe discontinuation. At the time of hospitalization, the patient's medications, comorbidities, and a measure of frailty will be entered into the software, which will generate an individualized and prioritized list of deprescribing opportunities to be considered as part of a deprescription plan.

## *2.2 Description of the intervention:*

A) Implement an electronic deprescribing tool (*MedSafer*) to guide physicians and pharmacists through the process of safe and successful medication deprescription and determine the impact on 30-day post-hospital discharge adverse drug events.

B) Using anonymized data collected through chart review:

1) Describe the population of patients admitted to medical clinical teaching units (CTUs) or general medical wards in terms of anonymous demographics, medication profiles, and select aggregate in hospital outcomes (emergency department visits and hospitalizations, falls, and re-admissions post-discharge).

2) Determine the proportion of medications taken by patients, which would be deemed potentially inappropriate at admission and discharge based on expert derived lists.

3) Determine if explicitly informing doctors that their patients are receiving medications which evidence-based guidelines suggest may be inappropriate reduces the use of these medications by facilitating and automating the deprescribing process during the intervention period.

A trained research assistant will use the electronic deprescribing tool, *MedSafer*, to rapidly screen and cross-reference eligible patients' medical conditions (extracted from the internal medicine admission note or consult note) against their active community medication list derived from the best possible medication history. This tool can only be accessed by authorized research staff and is encrypted with password protection.

Screenshots of each page of the tool are included at the end of protocol.

The electronic deprescribing tool compares the patient's medication and past medical history data against a composite ruleset which has been adapted by the investigators based on their expertise and on existing published criteria for safer prescribing and identifies those medications which are considered potentially inappropriate from the literature based on 1) risk of adverse drug event, or harm, relative to benefit or 2) lack of benefit or value.

In the control arm, all eligible participants will receive medication reconciliation at admission and discharge (current standard of care), and a structured follow-up phone interview to determine if they had an adverse event and adverse drug event within 30-days of hospital discharge. A prioritized deprescribing list will NOT be generated for patients during the control period of the study although the potentially inappropriate medications and any standard of care deprescribing decisions will be recorded.

During the intervention period, the medical teams will receive a printout with individualized and prioritized deprescribing opportunities: a) identifying the medication, b) explaining (with references and rationale) why that medication is potentially inappropriate and c) instructions on how to safely stop/taper the medication and what to look out for post discontinuation. The treating medical team will review these opportunities with the unit pharmacist and patient and subsequently appropriate candidate medications for deprescribing could be tapered or stopped by the most responsible physician on the CTU.

During the intervention period, for all patients who give consent for follow-up, the research assistants will provide a generic deprescribing brochure to inform them of the relevance of the study and the importance of medication review. Additionally, for those patients who are taking a proton pump inhibitor or a sedative hypnotic, they will receive corresponding patient-oriented educational material. The purpose of these brochures is to educate patients about the harmful effects of PPIs and sedative hypnotics. The patient brochures have been independently designed by the Canadian Deprescribing Network with input from patient stakeholders and the information is presented in lay terms in both French and English. Copies of each of the brochures are available online.

Proton pump inhibitors: <http://www.criugm.qc.ca/fichier/pdf/PPI-EN-Men.pdf>

Sedative hypnotics/sleeping pills: <http://www.criugm.qc.ca/fichier/pdf/BENZOeng.pdf>

### *2.3 Summary of findings from clinical studies that have potential implications:*

Updated from the MedSafer pilot study: polypharmacy, or the concurrent use of multiple medications, is common, costly, and harmful. As many as 40% of community-dwelling older adults are regularly prescribed five or more medications, despite being a population that is particularly vulnerable to adverse drug events (ADEs). Although several consensus-derived lists of potentially inappropriate medications (PIMs) for older adults exist that can be used as reference guides for comprehensive medication reviews, these lists can be challenging to translate into everyday practice. Lists of PIMs may not be applicable on an individual patient level and the process of cross-referencing multiple medications and medical conditions for the large number of patients who could benefit requires a command of the literature and is time consuming. Previously described strategies to address polypharmacy have demonstrated

variable efficacy, with interventions led by pharmacists having the greatest success. Nevertheless, interventions can be limited by cost, time constraints, and the need for expert personnel who may be in short supply.

#### *2.4 Summary of known potential risks and benefits:*

Few studies have specifically looked for safety events related to deprescribing or “adverse drug withdrawal event” (ADWEs). Most studies of deprescribing have been underpowered to detect an impact on ADEs. This study will add important data to the generation of evidence in favour of deprescribing in acute care from a safety and efficacy point of view. Potential benefits include a reduction in pill burden, direct and indirect medication related costs, improved quality of life, and a reduction in adverse drug events. Potential harms include ADWEs (e.g., seizure after abrupt discontinuation of a benzodiazepine or gastrointestinal bleeding following cessation of a proton pump inhibitor).

#### *2.5 Justification of the intervention:*

Using the abstracted patient data, the web-based tool will identify medications which are (a) at high risk of an adverse drug event, (b) at intermediate risk of adverse drug event or for which clinical judgement is required or (c) are of expected to be of little added benefit or value. It will generate a prioritized and individualized list of potentially inappropriate medications and recommendations on how to safely discontinue or taper medications. These deprescribing opportunities are given to the patient’s treating team for consideration (the CTU senior resident and unit pharmacist both receive a copy). This list is customized to the patient based on their medical history and the list of medications they are taking at admission. To avoid confusion or error on behalf of the treating teams (who have many patients under their care), the report is personalized with the patient’s identifying information on the reports/recommendations. This will also allow for transmission of the medication changes after discharge to the patient’s identified usual treating physician(s) and to their usual pharmacist(s) to avoid post-discharge medication errors from medication reconciliation.

The ruleset was derived from an expert consensus review of published or publicly available materials on safer drug use in older adults as well as from individual articles on specific medications and their risk of potential harm in the elderly.

Physicians (experts in geriatrics or those active in the field of “deprescribing”) and pharmacists (particularly geriatric pharmacists) are already performing many of these acts implicitly. This is, in general, considered the standard of care in geriatric medicine. However, not all physicians/pharmacists who take care of older adults have a command of the literature, and the identification of potentially inappropriate medications can be complex when a given patient has numerous medical comorbidities and is taking multiple medications.

Competing priorities for healthcare providers restrict the time available for in-depth medication reviews and many teams across Canada do not have easy access to an expert in geriatric pharmacy. The purpose of our study is to provide support in terms of a rapid evidence-based and personalized screening of the patient's history and medications to contribute to safer prescribing in older patients.

It is our belief that the overall quality of prescribing on the units involved will increase, and our hope is that trainees will continue to practice safe prescribing through repeated exposure to the rulesets. This is one of the major goals/benefits of our project and why we were particularly interested in working on medical clinical teaching units across Canada.

#### *2.6 Description of the population to be studied:*

Consecutive adults aged 65 years and older on five or more usual home medications admitted to one of the study units at the participating hospitals. Participants are expected to have a prognosis of greater than three months, as judged by the treating team.

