## Section 4: Trial Design

*4.1 A specific statement of the primary endpoints and the secondary endpoints, if any, to be measured during the trial.*

*Primary outcome:* Any adverse drug event within 30-days of hospital discharge (as defined by a 5 or 6 on the Leape and Bates scale). ADEs could include adverse drug withdrawal events (ADWEs).

*Secondary outcomes:*

- Proportion of patients with one or more PIM discontinued at discharge
- Absolute number of medications at discharge
- Absolute number of PIMs at discharge
- Adverse drug withdrawal events within 30-days post discharge
- Absolute number of medications at 30 days post-discharge
  - Proportion of medications that remain deprescribed at 30 days post-discharge
- Adverse events within 30-days post discharge
  - 30-day readmissions (ER or hospitalization) within 30-days post discharge
  - 30-day mortality in those that survive to hospital discharge
  - Falls within 30-days of hospital discharge
- 30-day post-discharge sleep questionnaire responses
- 30-day self-reported health-related quality of life

*Sensitivity analyses:*

- Adverse drug events as defined by a 4,5 or 6 on the Leape and Bates scale

*Effect by:*

- Biological sex
- Admission from a long-term care home
- Palliative status
- Frailty status (dichotomized as moderate to severely frail vs not)

*4.2 A description of the type/design of trial to be conducted (e.g., double-blind, placebo-controlled, parallel design) and a schematic diagram of trial design, procedures, and stages.*

This is a cluster randomized trial comprising 3 clusters: Quebec, Ontario, and Western Canada (Alberta and British Columbia).

*4.3 A description of the measures taken to minimize/avoid bias, including:*

(a) Randomization

The order that the cluster enters intervention is randomized prior to the start of the study.

(b) Blinding and Allocation Concealment

Study sites will only learn that they are crossing over to the intervention 4 weeks prior.

Healthcare personnel and patients at participating sites will remain blinded to the specific objectives of the study while in the control phase. They will be aware that we are conducting a study of post-discharge adverse events; however, they will not know that we are specifically looking at medication appropriateness, deprescribing, and adverse drug events. When study sites cross into intervention it will no longer be possible to blind them to the objectives.

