#### *5.1.b Subject exclusion criteria:*

- Expected to die within 1-3 months
- Patient or proxy do not speak English or French
- Did not provide consent
- No provincial health insurance
- Will be unable to reach by telephone post-discharge
- Taking fewer than five usual home medications
- Admission or transfer to a non-study unit is expected: patients who are ultimately discharged from non-study units during their hospitalization will be excluded unless that unit is a transitional care, rehabilitation, or post-acute care unit used to bridge the gap between acute medical hospitalization and community services. For example, patients transferred to and subsequently discharged from a surgical unit (where there is no intervention) will be excluded.

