##### - Proportion of patients with one or more PIMs stopped at discharge

A mixed-effects logistic regression model will be used for the outcome of stopping 1 or more PIM which controls for intervention, time period, and number of baseline potentially inappropriate medications as fixed effects and cluster as a random effect. This model will be

used to estimate adjusted risk differences. This analysis will be conducted on patients who are taking 1 or more PIM at admission and who are discharged alive from a study unit.

- ER Visit/Readmission within 30-days of hospital discharge

A mixed-effects logistic regression model will be used for the outcome of ER visit or readmission post discharge which controls for intervention, time period, frailty status, long-term care residence, age, gender and number of baseline potentially inappropriate medications as fixed effects and cluster as a random effect. This analysis will be conducted on patients who have consented to, and participated in, the post-discharge follow-up.

- Deaths within 30-days of hospital discharge

A mixed-effects logistic regression model will be used for the outcome of death post discharge which controls for intervention, time period, frailty status, HOMR score and number of baseline potentially inappropriate medications as fixed effects and cluster as a random effect. This analysis will be conducted on patients who have consented to, and participated in, the post-discharge follow-up.

- Falls within 30-days of hospital discharge

A mixed-effects logistic regression model will be used for the outcome of fall post discharge which controls for intervention, time period, frailty status, long-term care residence, age, gender and number of baseline potentially inappropriate medications as fixed effects and cluster as a random effect. This analysis will be conducted on patients who have consented to, and participated in, the post-discharge follow-up.

- Absolute number of medications at discharge

A generalized linear regression model will compare the number of medications at discharge controlling for intervention, time period, and the number of baseline medications as fixed effects and cluster as a random effect. This analysis will be conducted on all patients who are discharged alive on a study unit (see above re transitions of care).

- Absolute number of medications at 30 days post-discharge

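### The treating team judges the prognosis criterion and loses its blinding at crossover, so case-mix could shift with the intervention, and the primary ADE model has no frailty or prognosis covariate

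*Protocol*

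**What the plan says.** **Who judges prognosis.** Protocol Section 2.6 describes the population as "Consecutive adults aged 65 years and older on five or more usual home medications" and adds: "Participants are expected to have a prognosis of greater than three months, as judged by the treating team". The exclusion list in Section 5.1.b has "Expected to die within 1-3 months", with no assessor, instrument or threshold rule. The two wordings do not clearly describe the same cut.

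**What that team knows, and when.** Section 4.3(b) says: "Healthcare personnel and patients at participating sites will remain blinded to the specific objectives of the study while in the control phase". It continues: "When study sites cross into intervention it will no longer be possible to blind them to the objectives". On notice of the switch: "Study sites will only learn that they are crossing over to the intervention 4 weeks prior". Section 2.5 says that the report goes to the treating team: "the CTU senior resident and unit pharmacist both receive a copy".

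**What the analysis adjusts for.** The primary ADE model in Section 9.1a has intervention, time period and baseline PIM count as fixed effects and cluster as a random effect. The death model in the same section has "frailty status, HOMR score and number of baseline potentially inappropriate medications as fixed effects", besides intervention and period. Section 9.1a treats case-mix differences between phases as chance imbalances. Section 9.1b lists, among five post-hoc sensitivity analyses, one that adjusts for patient factors differing between groups at P < 0.01.

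**The concern.** Patients are identified and judged eligible one at a time, after their region's allocation is in force. Randomising the order of three regions does not protect against selection at this later step. One eligibility criterion is a clinical judgement by the people who receive the intervention, and their knowledge of the study changes at crossover. A team that knows enrolment brings a deprescribing report might keep a borderline patient in so as to get one, or leave the patient out as too near the end of life for it to matter.

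The patients affected would be those with the poorest prognosis, whose ADE risk may well differ from the average. A shift that arrives with the intervention is carried by the intervention term, so the period term cannot take it out. At stake is whether part of an observed ADE difference, or part of a missing one, reflects who was enrolled.

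**Working it through.** **Inputs from Protocol Section 9.2 (revised design) and Section 9.3.** Control ADE rate 15%; detectable difference 4.8 points; at least 80% power; 3 clusters, 4 periods, 500 patients per cluster-period (3 × 4 × 500 = 6000); intra-cluster correlation 0.01 to 0.05; alpha 0.05, taken as two-sided.

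**Step 1: reproduce the design.** The Hussey and Hughes variance of the intervention effect is

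v = I·s·(s + T·t) / [(I·U − W)·s + (U² + I·T·U − T·W − I·V)·t]

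with I = 3, T = 4, U = 3 + 2 + 1 = 6, W = 0 + 1 + 4 + 9 = 14 and V = 9 + 4 + 1 = 14. Total variance is 0.15 × 0.85 = 0.1275. At correlation 0.03, t = 0.03 × 0.1275 = 0.003825 and s = 0.97 × 0.1275 / 500 = 0.000247. Then v = 0.000294, so SE = 1.71 points. Power for 4.8 points is Φ(4.8/1.71 − 1.96) = about 80%. Over correlations 0.01 to 0.05 the SE is 1.70 to 1.72 points and power is 79.9% to 80.6%. The stated design reproduces and is not in dispute.

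**Step 2: spurious difference under no true effect.** Let a share f of otherwise eligible patients, with ADE risk h, be excluded only after crossover. The remaining risk is (0.15 − f·h)/(1 − f), so the drop is f·(h − 0.15)/(1 − f). The documents give neither f nor h; both are assumptions.

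| Extra excluded, f | h = 20% | h = 25% | h = 30% |
|---|---|---|---|
| 1% | 0.05 | 0.10 | 0.15 |
| 2% | 0.10 | 0.20 | 0.31 |
| 5% | 0.26 | 0.53 | 0.79 |
| 10% | 0.56 | 1.11 | 1.67 |

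Drops are in percentage points. The smallest is 0.05/4.8 = 1% of the target and the largest is 1.67/4.8 = 35%. If h = 15%, the drop is zero. If such patients are additionally included after crossover, the sign reverses.

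**Step 3: effect on the test.** With bias b and SE 1.7 points, two-sided error is Φ(−1.96 − b/1.7) + Φ(−1.96 + b/1.7). This gives 5.0% at b = 0.05, 5.2% at 0.20, 6.1% at 0.53, 10.0% at 1.11 and 16.6% at 1.67.

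**Step 4: what the model would absorb.** A shift present in every post-crossover cell and absent before it has the same pattern as the intervention indicator, so period and cluster terms leave it in the intervention estimate. Baseline PIM count removes only the part of the shift that it predicts. Frailty and HOMR score, which bear more directly on prognosis, are in the death model but not in the ADE model.

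**The case against.** The mechanism is possible but not evidenced. Nothing in the protocol suggests that teams would judge prognosis differently after crossover. Their incentive looks weak: Section 6.1 leaves them free to act on the report or not, and Section 4.5 calls the intervention low risk. Enrolment is consecutive and a research assistant enters the data. The operative exclusion list names no assessor; the treating-team wording stands in the background section. The change in knowledge is also not a clean switch, since control-phase staff know that a study of post-discharge adverse events is running and sites learn of crossover four weeks ahead. All this stands. It limits the discretion but does not remove it, because the prognosis filter still applies to consecutive patients.

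Some safeguards exist. Baseline characteristics are compared by phase, frailty and palliative status are listed for subgroup effects and so must be recorded, and the P < 0.01 sensitivity analysis would adjust for a marked shift in a measured factor. That also stands. But this adjustment is post hoc and triggered by a significance threshold, so a moderate imbalance could go unadjusted. Blinded adjudication protects outcome assessment, not enrolment.

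A reader might infer that the ADE comparison is biased by a point or more. The documents do not support that: the larger entries in the table need 10% of all otherwise enrolled patients to change status, in one net direction, through borderline prognosis calls alone. A reader might also infer that HOMR should replace clinical judgement as the eligibility rule. The documents do not support that either. They name HOMR only as a covariate in the death model and give no definition, prediction horizon, cut-off or availability at screening.

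**Conclusion.** The point holds as a weakness of design and adjustment, not as a demonstrated bias. The protocol states both premises: a subjective prognosis judgement by the treating team, and blinding of that team to the objectives that ends at crossover. The planned primary analysis would not fully remove a resulting shift in case-mix.

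Size and direction cannot be derived from the documents. Under the assumed 1% to 10% extra exclusion and 20% to 30% ADE risk, the spurious difference runs from about 0.05 points, which is negligible, to about 1.7 points, roughly a third of the 4.8-point target. It could favour or mask the intervention. Separately, the prognosis wording in Sections 2.6 and 5.1.b needs to be reconciled whatever the size of the bias.

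**What to change.** - **Section 9.1a, primary outcome:** add HOMR score and frailty status as fixed effects in the ADE model, using baseline values in both phases. Both are already covariates in the death model.
- **Reporting:** tabulate prognosis exclusions, and baseline frailty and HOMR, by region and period where screening records allow, so that a shift at crossover can be seen.
- **Sections 2.6 and 5.1.b:** reconcile the prognosis wording, name who applies it, and state that it is applied identically in both phases. Which threshold is meant is for the investigators. Do not impose a HOMR cut-off as an eligibility rule.

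Section 9.1b describes post-hoc analyses in the past tense, so new wording cannot change who was enrolled. The adjusted model and the tables remain usable. If the model is added after outcome data were seen, label it so under Section 9.6 and show it beside the model now in the plan.

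The cost is two more covariates, any missing values they bring, and one table. Adjustment reduces the bias but may not eliminate it, because a clinician's judgement can draw on information that neither measure captures.
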